### Secondary Outcome Measures

Secondary outcomes include momentary measurements of mood, energy, and sleep using simple visual analog scales ranging from 0 (worst) to 100 (best) at weekly intervals. Changes in these scales will be correlated with the type of apps selected, goals set, and duration spent within the OWC. There is evidence that depression is a significant covariate in analyses of changes in well-being in multiple studies [16,19,42]. Participants who score below 50 for mood in the visual analog scale will be invited to undergo a screening for depression using the Center for Epidemiologic Studies Depression Scale (CESD)[43,44]. Changes in well-being of this subset will be correlated with improvement in depression. To facilitate the cost-effectiveness analysis, data on health-related quality of life will be collected using the Assessment of Quality of Life-four dimensions (AQOL-4D) index [45]. The AQOL-4D includes four dimensions, namely, independent living, mental health, senses, and relationships. Each dimension has three items and ranges from -0.04 to 1.00 with higher score indicating better quality of life. The AQOL-4D is a self-completed questionnaire that can be administered online.

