### Study Design

This is a standard parallel arm clinical trial comparing the effectiveness and cost effectiveness of control and intervention arms offered over 4 weeks. Group 1 represents the intervention arm (OWC with The Toolbox) and Group 2 represents the waitlist control arm (OWC without The Toolbox). In this study, participants in the intervention arm will be able to access the active component of the trial, The Toolbox, through the OWC straight away. Participants in the control group will gain access to The Toolbox after 4 weeks. Once participants follow the online links as described in the recruitment section, they will be directed to the project’s landing page (Figure 1). Once there, they will be required to complete the steps outlined in Figure 4.

All participants will receive regular SMS and email prompts from the OWC to remind them to complete study measures. As detailed in Table 1, assessments will be administered at sign up, and at 4 weeks. In addition, participants will be prompted to regularly monitor their mood, energy and sleep.

**Table 1 table1:** Assessment scales administered at each time point during the study.

Instrument	Measurement	Baseline	After 4 Wk
Mental Health Continuum Short Form	Well-being/Positive mental health	X	X
Center for Epidemiologic Studies Depression Scale	Symptoms of depression	X	X
Assessment of Quality of Life-four dimensions index	Quality of life data	X	X
Resource use questionnaire	Cost effectiveness		X
Demographics	Date of birth, gender, postcode, employment, education, cultural background, and living conditions	X	
Heuristic well-being questions	Feelings, energy, and sleep	Weekly	Weekly

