### Sample Size

The primary outcome measure is change in well-being as measured by MHC-SF. A total of 180 completed participants (90/arm) are required to provide 80% power to detect a difference of 0.37 in improvement between arms with a two-tailed type 1 error of 0.05. This assumes an overall standard deviation of 0.63 at baseline and 0.81 at 1-month follow-up as found in Bolier et al [16], and a conservative correlation of 0 between baseline and follow-up scores. Considering the higher attrition level found by Bolier et al [16] (37.8%) this study will aim to recruit a sample of 250 participants.

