### Statistical Analysis

The primary analysis is based on intention to treat, and missing values from all randomized participants will be imputed with 50 samples redrawn from the original data. The primary outcome will be assessed using random effects mixed modeling, with the well-being score as the dependent variable. The independent variables are time, group, and the time × group interaction (product) term, which are clustered over age, gender, geographical location, work status, cultural background, education level, and living circumstances to account for possible correlated readings. Sensitivity analyses and secondary continuous outcomes will be assessed similarly, but also adjusted for potential confounders. All results will be reported with 95% CI and *p* values. A *p* value < 0.05 (two tailed) was taken to be significant. All analyses will be performed using Stata version 13.1 (College Station, TX, USA) [46].

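### The primary model leaves out baseline mood, and the article does not say that the weekly mood, energy and sleep ratings inform the imputation; the likely cost is a modest loss of precision

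*Protocol article*

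**What the plan says.** All references are to the Protocol article.

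- **Secondary Outcome Measures:** "There is evidence that depression is a significant covariate in analyses of changes in well-being in multiple studies". The CES-D is then offered only to participants whose mood rating falls below 50. The mood, energy and sleep scales carry no such restriction.
- **Study Design:** "participants will be prompted to regularly monitor their mood, energy and sleep". Table 1 marks these questions as weekly in both the baseline and the 4-week columns. The MHC-SF is taken only at baseline and week 4.
- **Statistical Analysis, primary model:** "The independent variables are time, group, and the time" by group product, with a list of demographic factors over which the terms are said to be clustered. No depression or mood term appears. Adjustment for confounders, which are not named, is kept for sensitivity analyses and secondary outcomes.
- **Statistical Analysis, missing data:** "missing values from all randomized participants will be imputed with 50 samples redrawn from the original data". No imputation predictors are listed.
- **Sample Size:** attrition of 37.8% is taken from an earlier trial of an online well-being intervention.
- **Limitations:** completion of secondary measures is neither required nor guaranteed.

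**The concern.** The article names depression as a predictor of the quantity that the primary analysis estimates, then fixes a primary model without it or any stand-in. The CES-D cannot fill the role, because only an invited low-mood subset receives it. The baseline mood rating is the nearest measure scheduled for all participants.

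The imputation raises a related point. With only two MHC-SF assessments, a participant who leaves before week 4 has no later well-being score. The weekly ratings, together with usage of the Online Wellbeing Centre (OWC), are the scheduled information on that person after randomization. If the imputation ignores them, some precision is lost. If dropout follows mood differently in the wait-list and Toolbox arms, the imputed difference is also biased although data that could reduce the bias are held.

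**Working it through.** **Inputs from the article.** Difference 0.37; SD 0.63 at baseline and 0.81 at follow-up; correlation 0 between them; 90 completers per arm; two-sided 5%; attrition 37.8%; 250 recruited; MHC-SF test-retest reliability 0.68 over 3-month periods.

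**Assumptions, because the article gives no figures.** Partial correlation p of baseline mood with MHC-SF change: 0.14 to 0.4. Partial correlation rho of the interim ratings with week-4 MHC-SF, given baseline: 0.3 to 0.5. Fraction f of dropouts who left a reading: 0.4 to 0.8.

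**1. The plan's own figure.** SD of change = sqrt(0.63² + 0.81²) = 1.026. Completers per arm = 2 × (1.960 + 0.842)² × 1.026² / 0.37² = 120.7, so 121. The stated 90 per arm gives 67.7% power with these inputs; 80% at 90 per arm needs a correlation of about 0.26. The mismatch is a separate matter. It serves here only as the starting point for the precision calculation.

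**2. Baseline mood in the model.** With two complete waves, time × group is the between-arm difference in change. A covariate entered only as a main effect drops out of the change. In a simulated complete dataset of 180, adding depression as a main effect left the standard error at 0.1193. Adding its time interaction gave 0.1196, because in that dataset depression was almost equally related to both waves and so hardly predicted change. A gain therefore needs the time interaction, and a covariate that predicts change. Where it does, variance is multiplied by 1 − p²:

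| p | Variance factor | SE reduction | Power at 90 per arm, correlation 0 |
|---|---|---|---|
| 0 | 1.00 | 0% | 67.7% |
| 0.14 | 0.98 | 1% | 68.5% |
| 0.2 | 0.96 | 2% | 69.4% |
| 0.3 | 0.91 | 4.6% | 71.8% |
| 0.4 | 0.84 | 8.3% | 75.1% |

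If the baseline to follow-up correlation is 0.65, power at 90 per arm is already 97.8%, so the gain matters less.

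**3. Interim ratings as auxiliaries, no differential dropout.** With m = 0.378, the variance ratio is [(1 − rho²)/(1 − m) + rho²/(1 − m + m·f)] × (1 − m).

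- rho = 0.3, f = 0.4: 0.91 + 0.09 × 0.622/0.773 = 0.982.
- rho = 0.5, f = 0.8: 0.75 + 0.25 × 0.622/0.924 = 0.918.

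This is a variance reduction of about 2% to 8%.

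**4. Differential dropout.** A large-sample simulation used follow-up SD 0.81, a true difference of 0.37, 37.8% missing, baseline to follow-up correlation 0.5 to 0.68 and rho 0.3 to 0.5. In controls only, the odds of dropout rose 1.65 to 2.7 fold per SD of lower mood.

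- Imputing from arm and baseline MHC-SF: estimate 0.26 to 0.34.
- Adding the rating, with a reading from every dropout: about 0.37.
- Adding the rating, with a reading from 40% of dropouts: 0.32 to 0.35.
- Half the mood dependence also present in the Toolbox arm: 0.32 to 0.35 without the ratings, 0.35 to 0.36 with them.
- The same dependence in both arms: no bias.

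For scale, 250 × 0.622 = 155.5 completers, about 77.75 per arm. The baseline-adjusted SE is 0.81 × sqrt(1 − r²) × sqrt(2/77.75) = 0.113 at r = 0.5 and 0.095 at r = 0.68.

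**The case against.** A randomized comparison without covariates is valid, and adjusted sensitivity analyses are already planned. The sentence on depression introduces CES-D screening and a correlation analysis in that subset; it does not promise a depression term in the primary model. Using a single mood rating as a stand-in for depression is the reviewer's proposal, not the plan's. All of this stands. There is no contradiction and no invalid test, only an efficiency choice that could be better.

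Three stronger readings are tempting, and the article does not support them:

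- **That the imputation excludes the ratings.** The article lists no predictors, so it neither includes nor excludes them, and such a list is commonly left to the full plan.
- **That the ratings will exist for everyone.** They are scheduled and prompted, but the Limitations section says completion is not assured.
- **That they are the only data on dropouts after randomization.** The article also plans to use apps selected, goals set, time in the OWC and visits to it.

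The bias figures also need mood-driven dropout that differs by arm. Nothing in the article shows this, and the largest figures place it in one arm only.

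What survives is that the primary model is stated explicitly, and baseline mood is not in it. Under planned attrition near 38%, naming the auxiliaries is a concrete and nearly free improvement.

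**Conclusion.** The point holds as an improvement to the analysis, not as an error that invalidates it. The expected gain is modest: a standard error about 1% to 8% lower from baseline mood (partial correlation 0.14 to 0.4), and about 2% to 8% less variance from the auxiliaries (partial correlation 0.3 to 0.5, with 40% to 80% of dropouts leaving a reading). All these correlations and fractions are assumed.

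Protection against bias is a possible further benefit. It is conditional on mood-related dropout differing between arms, and it would be complete only if every dropout left a reading. A reader might take 0.26 to 0.34 against 0.37 as the expected bias; it is a scenario range and no more.

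**What to change.** Amend the Statistical Analysis section in two places before the data are analyzed.

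1. **Primary model.** Add the baseline mood rating together with its interaction with time, since a main effect alone does not change the standard error of time × group. Impute missing baseline mood so that no randomized participant is lost.
2. **Imputation.** State that the available baseline and weekly mood, energy and sleep readings, and OWC usage, enter the imputation of week-4 MHC-SF as auxiliary variables, by arm. Keep everything measured after baseline out of the analysis model, because the intervention may affect it.

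The cost is some analysis wording and code, and no new data. The gain will be partial, because some dropouts will have left no reading.

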**Methods:**

This study will be a two-arm, randomized controlled trial following a wait-list control design. The primary outcome will be changes in psychological well-being measured by the Mental Health Continuum Short Form. The secondary outcomes will be drawn from a subsample of participants and will include depression scores measured by the Center for Epidemiologic Studies Depression Scale, and quality of life measured by the Assessment of Quality of Life-four dimensions (AQOL-4D) index. Cost-effectiveness analysis will be conducted based on a primary outcome of cost per unique visit to the OWC. Utility-based outcomes will also be incorporated into the analysis allowing a secondary outcome to be cost per quality-adjusted life year gained (based on the AQOL-4D values). Resource use associated with both the intervention and control groups will be collected using a customized questionnaire. Online- and community-based recruitment strategies will be implemented, and the effectiveness of each approach will be analyzed. Participants will be recruited from the general Australian population and randomized online. The trial will last for 4 weeks.

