### Randomization

Randomization will occur in blocks of four to ensure approximately equal numbers in each arm. Participants will be asked to read the study information and give their consent online. They will then be directed to create a password-protected account to login to the OWC. After login, participants will be randomized into two groups. The intervention group will have immediate access to The Toolbox, whereas the control group will be allocated to the wait-list for 4 weeks.

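### The depression scale is triggered by a weekly mood score with no reading specified, so post-randomisation mood may decide who has CES-D data and some may lack a baseline

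*Protocol article*

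**What the plan says.** Four places in the protocol article bear on who completes the CES-D and when.

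- **Secondary Outcome Measures** makes it conditional: "Participants who score below 50 for mood in the visual analog scale will be invited to undergo a screening for depression". The mood scale is recorded "using simple visual analog scales ranging from 0 (worst) to 100 (best) at weekly intervals". No reading is named as the trigger. The planned use is then given: "Changes in well-being of this subset will be correlated with improvement in depression".
- **Study Design** says "assessments will be administered at sign up, and at 4 weeks". Table 1, captioned "Assessment scales administered at each time point during the study", has a CES-D row ("Symptoms of depression") marked at both times, with no footnote. It lists the mood, energy and sleep questions as weekly.
- **Abstract, Methods**: "The secondary outcomes will be drawn from a subsample of participants and will include depression scores". It gives no rule for forming the subsample.
- **Randomization**: "After login, participants will be randomized into two groups". Weekly mood readings therefore continue after allocation.

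Statistical Analysis adds that secondary continuous outcomes are handled like the primary one, that is, by the model with a time × group term.

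**The concern.** Mood is listed as a secondary outcome, and the Primary Outcome Measure section treats change in the mood, energy and sleep trackers as a sign of behavioural change. If a mood reading taken after allocation can trigger the CES-D, a variable the intervention is meant to move helps to decide who has depression data. The two arms' CES-D subsets may then no longer be comparable, and adjusting for baseline confounders does not restore the comparison.

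There is also a gap in the data. Improvement in depression needs a CES-D score at both times. A participant first scoring below 50 in week 2, say, was not invited at sign-up and has no baseline score, so neither the change correlation nor the time × group model has the pair it needs.

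This is a rule for collecting data, built into the website. An analysis plan written later cannot recover scores that were never taken.

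**Working it through.** **Step 1: the text side by side.**

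| Question | Secondary Outcome Measures | Study Design and Table 1 | Abstract |
|---|---|---|---|
| Who gets the CES-D? | Mood below 50 | No restriction shown | A subsample, no rule |
| When? | On invitation, no time given | Baseline and 4 weeks | Not stated |
| Which mood reading triggers? | Not stated; scale is weekly | Not stated; scale is weekly | Not stated |

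The three can be read together only by adding something none of them says: that the sign-up reading is the trigger and that everyone invited then is measured again at 4 weeks.

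**Step 2: how much the unstated rule could matter.** The plan has no figure to reproduce, because the documents give no mood or CES-D distribution. Every input here is an assumption:

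- mood mean 60, SD 20
- correlation between any two mood readings r = 0.5 to 0.65
- CES-D/mood correlation 0.7 in size (higher CES-D is worse)
- true effect 0.45 SD on both CES-D and mood, the mood effect building linearly over 4 weeks
- five readings: sign-up and weeks 1 to 4

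*One case by hand.* Suppose only week-4 mood below 50 gives a CES-D. Let c = (50 − 60)/20 = −0.5, δ = 0.45 and λ(x) = φ(x)/Φ(x). A control is selected if standardised mood is below c. An intervention participant is selected if the mood they would have had without the Toolbox is below c − δ = −0.95. The observed CES-D difference is

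−δ + 0.7 × [λ(c − δ) − λ(c)]

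λ(−0.5) = 0.3521/0.3085 = 1.141 and λ(−0.95) = 0.2541/0.1711 = 1.485, so the difference is −0.45 + 0.7 × 0.344 = −0.21 SD.

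*All rules by simulation* (2,000,000 draws per scenario, true difference −0.45 SD):

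| Who has a 4-week CES-D | Arm difference (SD) | Loss |
|---|---|---|
| Everyone | −0.45 | none |
| Baseline mood below 50, all followed | −0.45 | none |
| Any weekly reading below 50, all followed | −0.40 to −0.41 | about 10% |
| Baseline below 50 and week-4 mood below 50 | about −0.24 | about half |
| Week-4 mood below 50 only | about −0.21 | about half |
| Any of these rules, mood unaffected by the Toolbox | −0.45 | none |

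Under the fourth rule, of those below 50 at baseline, 53-61% of controls but only 34-40% of the intervention arm would have a 4-week CES-D.

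Under the any-week rule, 43-49% of those triggered were at or above 50 at sign-up and so have no baseline CES-D (38-44% in the intervention arm, 47-52% in the control arm).

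**Step 3: sensitivity.** With selection on a single post-randomisation reading, mood means of 55 or 65 and CES-D/mood correlations of 0.5 or 0.7, a true 0.20 SD becomes 0.09-0.13 SD and a true 0.46 SD becomes 0.21-0.30 SD, a loss of roughly 35-55%. A baseline trigger recovers the true value throughout.

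**The case against.** **Table 1 shows when, not who.** This stands. Its resource-use row is also unqualified, although Subsidiary Outcome Measures limits that questionnaire to 50 participants, and the Abstract already says subsample. A reader might infer that Table 1 gives the CES-D to every participant and so flatly contradicts the mood threshold. The documents do not support that. What remains is a restriction the table does not carry and a baseline CES-D that a later trigger cannot supply.

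**Nothing says improvers are dropped.** This also stands. A reader might infer that someone whose mood rises above 50 is not asked for the 4-week CES-D. No section says so, and the planned correlation needs repeat scores, which argues against it. The halving in the table belongs to that reading alone.

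**A sign-up trigger may be what was meant.** Possibly. Selection on a pre-randomisation reading would cause no bias between arms, and Figure 4, not available here, may show the order of steps. But the text does not say it.

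**The harm is limited.** Largely true. The only CES-D analysis named in Secondary Outcome Measures is a correlation within the subset; the arm comparison is implied by the general sentence in Statistical Analysis. The primary MHC-SF analysis is untouched. The assumed 0.45 SD is also large for a trial that expects small gains.

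**A condensed article may leave this detail out.** That would excuse silence. Here the article does state the trigger, but on a repeated measure without a time.

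**Conclusion.** The point holds as a defect in how the CES-D set is defined. The trigger is not tied to the pre-randomisation mood score, so the protocol permits, but does not require, selection on a post-randomisation outcome. The Abstract, Study Design with Table 1, and Secondary Outcome Measures need reconciling.

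The size depends on a rule the documents do not give. With the assumed inputs, bias in the arm difference runs from none (baseline trigger, or no effect on mood), through about 10% (any weekly reading, all followed), to about half (re-gated on week-4 mood). The last figure also needs mood itself to shift by 0.45 SD and should not be quoted as the expected loss. The missing baseline scores do not depend on any effect on mood: under an any-week trigger, roughly 40-50% of those triggered would lack one. As this is a secondary outcome, the sponsor should correct it, but the primary conclusion is not at risk.

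**What to change.** 1. In Secondary Outcome Measures, define the CES-D analysis set by the mood score taken at baseline, and state that this reading precedes randomisation.
2. Collect the CES-D from all of that set at baseline and again at 4 weeks, whatever their later mood.
3. Add a footnote to the CES-D row of Table 1 giving this restriction, and use the same definition for the Abstract's subsample.
4. If screens triggered by later mood readings are offered, keep them out of both the arm comparison and the change correlation.

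The cost is a trigger setting on the website, a sentence and a footnote, and a few more CES-D completions at 4 weeks.

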### Subsidiary Outcome Measures

Resource use associated with both the intervention and control groups will be collected from a sample of 50 participants at the end of the trial using a resource use questionnaire. This is a custom questionnaire developed by the funding body Young and Well CRC and includes questions corresponding to the period of the trial on participants’ employment/education status, wages, their use of health services (type and duration), number of times (and duration) they accessed the OWC and other mental-health-related Internet sites, and how much they pay to access the Internet.

### Sample Size

The primary outcome measure is change in well-being as measured by MHC-SF. A total of 180 completed participants (90/arm) are required to provide 80% power to detect a difference of 0.37 in improvement between arms with a two-tailed type 1 error of 0.05. This assumes an overall standard deviation of 0.63 at baseline and 0.81 at 1-month follow-up as found in Bolier et al [16], and a conservative correlation of 0 between baseline and follow-up scores. Considering the higher attrition level found by Bolier et al [16] (37.8%) this study will aim to recruit a sample of 250 participants.

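### Recruiting 250 at the stated 37.8% attrition leaves about 155 completers, not the 180 that the sample size requires

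*Protocol article*

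**What the plan says.** The Sample Size section of the protocol article states the requirement in completers: "A total of 180 completed participants (90/arm) are required to provide 80% power". The target effect is "to detect a difference of 0.37 in improvement between arms" with a "two-tailed type 1 error of 0.05". The variability inputs are an "overall standard deviation of 0.63 at baseline and 0.81 at 1-month follow-up" and "a conservative correlation of 0 between baseline and follow-up scores".

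The same paragraph then moves from completers to recruits. It refers to the attrition seen in an earlier online well-being trial and concludes: "37.8%) this study will aim to recruit a sample of 250 participants". It gives no other attrition rate and no inflation formula.

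**The concern.** One paragraph fixes a number of completers, an attrition rate and a number of recruits. Any two of these determine the third, and the printed values do not fit together. If attrition reaches the rate the plan cites, the trial meets its recruitment target and still misses the number of completers it calls required. It would then run below its planned power for the primary outcome, although the abstract expects only small gains. A null result could be misread as evidence of no benefit.

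**Working it through.** **Inputs, all from the Sample Size section:** 180 completers (90 per arm); attrition d = 0.378; recruitment target 250; difference 0.37; two-sided alpha 0.05; SD 0.63 at baseline and 0.81 at follow-up; correlation 0.

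**Where 250 comes from**
- Correct allowance, N/(1 − d): 180/0.622 = 289.4, so 290. This does not give 250.
- Common slip, N × (1 + d): 180 × 1.378 = 248.0, which rounds to 250.

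The formula is not printed, so the slip is inferred from the match.

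**What 250 delivers**
- Completers: 250 × 0.622 = 155.5, or 77.75 per arm.
- Shortfall: 180 − 155.5 = 24.5, and 24.5/180 = 14%.
- Attrition at which 250 would leave 180: 1 − 180/250 = 28%. The article states no such rate.

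**Power with 77.75 per arm**

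Normal approximation: power = Φ(0.37/(SD × √(2/n)) − 1.96).

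1. *Accepting that 90 per arm gives 80%.* The implied SD is 0.37/((1.960 + 0.842) × √(2/90)) = 0.886. At 77.75 per arm the ratio of difference to standard error is 2.604, so power is 74%.
2. *Using the stated SDs and correlation 0.* The SD of change is √(0.63² + 0.81²) = 1.026. The standard error is 1.026 × √(2/77.75) = 0.1646 and the ratio is 2.248, so power is 61%. The difference detectable with 80% power is 2.802 × 0.1646 = 0.46.

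**Separating the two errors.** With an SD of 1.026, 90 per arm already gives only 68% power, and 80% needs 121 per arm (242 completers). The attrition step alone therefore costs 6 to 7 points: 80% to 74% on the first basis, or 68% to 61% on the second.

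**Baseline-adjusted analysis.** The residual SD is 0.81 × √(1 − r²).
- At r = 0 the SD is 0.81. The requirement is 2 × 0.81² × 2.802²/0.37² = 75.2, so 76 per arm (152 completers). Power at 77.75 per arm is 81%.
- At r = 0.65, the 9-month test-retest value in the Primary Outcome Measure section, the SD is 0.616 and power is 96%.

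**The case against.** Five points can be made for the plan.

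- **The cause is not documented.** No formula is given, 248 is not 250, and 250 is a round number. The authors may have had a lower rate in mind: the Results section foresees telephone follow-up, and the Limitations section argues that a short trial helps retention. It is fair to call the slip probable only. The shortfall does not depend on it, because 37.8% is the only rate offered and no lower one is stated or justified.
- **The 61% mixes two errors.** This stands. Only 6 to 7 points belong to the attrition step; the rest comes from the 90 per arm.
- **The planned analysis uses everyone randomized.** The Statistical Analysis section specifies imputation and a mixed model with a time by group term, so baselines from all 250 contribute. With 125 baselines and 77.75 follow-ups per arm at correlation 0, the variance is 2 × (0.63²/125 + 0.81²/77.75) = 0.0232. The standard error is 0.152 and power is 68%. This recovers about what the attrition step cost, but it is still below 80%. Nor does imputation turn missing outcomes into completers, the unit in which the requirement is stated.
- **Zero correlation is pessimistic.** This stands as mitigation. With 155 completers, a plain change-score analysis reaches 80% at a correlation of about 0.37 and 96% at 0.65. The plan, however, bases its claim on zero.
- **Nothing is biased.** True: estimates and type I error are unaffected. The fault lies in the recruitment target and the power claimed for it.

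**Conclusion.** The concern holds. With 37.8% attrition, 250 recruits give about 155 completers, not 180, and 180 completers need 290 recruits. The count rests only on the paragraph's own three figures.

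The power consequence depends on the basis: 74% if the plan's 90 per arm is taken at face value, and 61% (detectable difference 0.46) with its stated SDs and zero correlation. Both are normal approximations for a comparison of change among completers. Under the planned mixed model with all baselines, power at correlation 0 is about 68%. None of these reaches 80%. A correlation near the reported test-retest values would lift power well above 80%, but the plan does not rely on that.

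**What to change.** In the Sample Size section, state that 250 recruits at 37.8% attrition are expected to leave about 155 completers (78 per arm), and give the power for that number. Then choose one of these:

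- **Specify a baseline-adjusted primary analysis.** It needs 152 completers for 80% power at correlation 0, so the claim for 0.37 holds with 250 recruits. This also needs a matching change in the Statistical Analysis section.
- **Keep the change-score basis and restate the claim.** Power is then 61% for 0.37 with the stated SDs and correlation 0, or the detectable difference is 0.46.

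Raising recruitment to 290 would restore 180 completers but not 80% power under the stated inputs. That would take 242 completers, and 242/0.622 = 389.1, so 390 recruits. If the authors did plan on 28% attrition, they should say so and justify it; the error in the 90 per arm would remain.

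The cost is two corrected figures in one paragraph, plus the analysis wording if baseline adjustment is chosen. No extra recruits are needed, which matters because recruitment began in December 2014. Without baseline adjustment, the stated power becomes less favourable.
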